**Fig. 1 Fig1:**
[figure not shown]
Study design

### Study groups and methods of CAD screening

#### Screening group

Individuals who had at least one screening exam (stress electrocardiogram test, stress echocardiography, myocardial scintigraphy coupled with stress test or pharmacological stimulation using adenosine, or coronary CT scan) (Table 2) during the selection period (2008–2015).

**Table 2 Tab2:** Codes used to identify tests to screen coronary artery disease

Tests	Procedure codes
Stress test	DKRP004, EQRP002, EQRM001
Myocardial scintigraphy coupled with stress test or pharmacological stimulation using adenosine	DAQL001, DAQL010, DAQL011, DAQL009
Stress echocardiography	DAQM003, DZQM002, DBQM001
Coronary CT scan	ECQH010
Procedure codes: Codes of the French classification of medical procedure (CCAM)	

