DYNAMIT [12]	DT2M Age 55–75 years +$$\ge $$ 2 CV risk factors	2000–2003	3.5	All-cause death, non-fatal MI, non-fatal stroke, HH requiring hospitalization or visit to emergency department	631	54	5.5	2.4	1.00 (0.59–1.71)
FACTOR-64 [13]	T2DM + T1DM Men $$\ge $$ 50, Women $$\ge $$ 55 years diabetes duration $$\ge $$ 3 years or Men $$\ge $$ 40 years, Women $$\ge $$ 45y + Diabetes duration $$\ge $$ 5 years	2007–2013	4.0	All-cause death, nonfatal MI, or hospitalization for unstable angina	900	62	8	1.7	0.80 (0.49–1.32)
DADDY-D [14]	T2DM Age 50–70 years 10-year CV risk score ≥ 10%	2007–2012	3.6	Non-fatal MI or CV death	520	26	2.6	1.4	0.85 (0.39–1.83)

*T2DM* type 2 diabetes mellitus, *T1DM* type 1 diabetes mellitus, *CV* cardiovascular, *MI* myocardial infarction, *HH* heart failure

Despite this lack of evidence, most of guidelines recommend systematic screening for silent CAD in asymptomatic individuals with diabetes and high or very high cardiovascular risk [17–20]. Hence, a majority of physicians practice routine screening for silent CAD in patients with diabetes. We conducted a preliminary survey (unpublished data) in France in 2019 to determine the practices of 605 physicians in terms of screening for silent CAD in T2DM patients at a very high cardiovascular risk. A majority of participants (80% of cardiologists and 69% of diabetologists) reported a routine CAD screening practice with a sustained frequency: once a year (42%), once/2 years (20%), and once/3 years (33%).

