A routine CAD screening induces high healthcare expenses as it leads to invasive investigations, endovascular and surgical revascularizations as well as intensification of pharmacological therapies. To the best of our knowledge, the cost-effectiveness of routine CAD screening has not been evaluated prospectively in population with T2DM and a very high cardiovascular risk. Only two economic studies, based on Markov models, have addressed this question by comparing different strategies in Japanese and American populations: no screening, screening (with stress echocardiography, myocardial scintigraphy coupled with stress test, or stress electrocardiogram) [21, 22]. Their results were very limited by model’s hypothesis; uncertainty surrounding epidemiological and utilities data used; and costs of care, which may differ greatly across countries. In this context of discrepancy between lack of evidence and current guidelines and clinical practice, we aim to estimate the effectiveness and cost-effectiveness of systematic CAD screening in patients with T2DM and a very high cardiovascular risk.

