### Recruitment of participants and follow‑up

The data will be extracted from January 1, 2008 to December 31, 2019. A selection period will be defined by the 7 years (January 1, 2008 to December 31, 2014) preceding the index date. It will enable us to identify eligible patients and measure all the variables needed for the calculation of the high dimension propensity score (hdPS). Each participant will be assigned to one of the two study groups on the index date (January 1, 2015), and then followed up to December 31, 2019 (Fig. 1).

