#### No-screening group

Participants who never experienced a screening exam as described above during the selection period (2008–2015), except resting electrocardiogram.

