### Study endpoints

#### Primary endpoint

The incremental cost per life year saved over 5 years in CAD screening group *versus* no CAD screening.

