## Conclusions

SCADIAB study is the first investigation of the cost-effectiveness of CAD screening strategy in T2DM patients with a very high cardiovascular risk. It will evaluate the economic impact and clinical benefits of routine CAD screening in this population. It will also evaluate the clinical practice regarding CAD screening. SCADIAB will provide essential information for payers, clinicians, and scientific societies in terms of long-term efficiency of systematic CAD screening in a large T2DM population. Our study will also measure the economic performance of CAD screening in a real-world setting, with an accurate comparison with no CAD screening strategy. The SCADIAB findings will help to optimize the use of health care resources and guide clinical decision-making and future recommendations.

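### The primary ICER compares at least one past CAD test with none, while the aim and conclusions are about routine or systematic screening

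*Protocol article*

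**What the plan says.** The Background of the protocol article states the objective: "we aim to estimate the effectiveness and cost-effectiveness of systematic CAD screening in patients with T2DM and a very high cardiovascular risk". The Conclusions promise results on systematic screening for payers, clinicians and scientific societies, "with an accurate comparison with no CAD screening strategy". The Statistical analysis plan section adds a budget impact analysis of rolling out systematic screening.

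The Background also shows what routine means in practice. In the survey of 605 physicians, most respondents "reported a routine CAD screening practice with a sustained frequency: once a year (42%), once/2 years (20%), and once/3 years (33"%).

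The comparison itself is fixed as follows:

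- Window (Recruitment of participants and follow-up): "A selection period will be defined by the 7 years (January 1, 2008 to December 31, 2014) preceding the index date".
- Screening group: "Individuals who had at least one screening exam" in that period, with no minimum number or frequency.
- No-screening group: "Participants who never experienced a screening exam as described above during the selection period".
- Primary endpoint: "The incremental cost per life year saved over 5 years in CAD screening group" versus the no-screening group.
- Follow-up: patients are assigned on 1 January 2015 "and then followed up to December 31, 2019".

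Frequency appears in two other places. Clinical endpoints includes a description of exams per person per year. The Statistical analysis plan section defines four frequency subgroups to study the relation between screening frequency and survival; the lowest consists of patients with a single exam in follow-up.

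**The concern.** A screening programme is defined by repetition, and its costs and its effects both depend on how often people are tested. Under the arm definition, a patient with one isolated stress test in 2008 counts exactly as much in the primary ICER as a patient tested every year. The resulting ratio averages over an unknown mix of one-off and repeated testing.

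The result is nevertheless to be reported as evidence on routine or systematic screening and used to inform guidelines and payers. If the ratio is unfavourable, nobody can tell whether that reflects the programme or sparse testing. If it is favourable, it does not follow that a programme with an exam every one to three years would have the same ratio.

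**Working it through.** **The plan's own figure.** The only number under Sample size estimation is the eligible count. 2,400,000 × 0.38 × 0.10 = 91,200, which agrees with the stated minimum of 90,000. It gives no arm sizes and no distribution of exams.

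**Exams implied by routine practice.** Inputs are the survey shares (42%, 20%, 33%; Background) and the 7-year window (Recruitment of participants and follow-up).

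| Reported frequency | Share | Exams per year | Exams in 7 years |
|---|---|---|---|
| Yearly | 42% | 1 | 7 |
| Every 2 years | 20% | 0.5 | 3.5 |
| Every 3 years | 33% | 0.333 | 2.3 |
| Required for the screening arm | – | 1/7 = 0.143 | 1 |

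Weighted mean, counting the unreported 5% as zero: 0.42 × 1 + 0.20 × 0.5 + 0.33 × 0.333 = 0.42 + 0.10 + 0.11 = 0.63 per year, or 0.63 × 7 = 4.4 exams. Among the 95% reported: 0.63 / 0.95 = 0.66 per year, or 4.6 exams. The entry threshold is 0.143 / 0.333 = 43% of the slowest reported schedule.

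**What happens to the ICER.** Let a share s of the arm be tested only occasionally. Let routine testing have incremental cost C and life-year gain E against no testing, and occasional testing have a × C and b × E. Then

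pooled ICER / routine ICER = (1 − s + s·a) / (1 − s + s·b).

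If a = b, the ratio is 1 and the ICER is unchanged. With C and E positive and a and b between 0 and 1, the pooled ICER is higher than the routine one if a > b and lower if a < b. The documents give none of s, a or b, so neither direction nor size can be stated.

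**Whether the frequency subgroups repair it.**

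- Outcome: they are tied to survival. The article links neither cost nor the ICER to them.
- Window: the lowest class is counted over follow-up (2015–2019), whereas the arms are formed on 2008–2014. Classes formed after the index date also depend on surviving long enough to be tested again.
- Boundaries: moved to the 7-year window, the rates correspond to 7 or more exams, 4 to 6, exactly 3, and exactly 1. A patient with two exams (2/7 = 0.286 per year, below 0.333) fits no class.

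**The case against.** The best defence is that the contrast is stated openly. At least one exam versus none is a legitimate estimand, and systematic need not mean repeated: Table 1 applies the word to randomised trials without specifying an exam frequency. The survey reports what physicians say they do, so turning it into exams per patient assumes equal patient loads and full adherence to the stated interval. All of this stands, and it limits the point to a mismatch between label and exposure. It does not remove the mismatch, because the Background ties routine practice to a repeated schedule and the Conclusions carry the result over to that strategy.

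Three stronger readings are tempting, and the documents do not support them:

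- A reader might infer that the primary result is biased towards no effect by a calculable amount, for instance by shrinking the 20% relative risk reduction mentioned in the Discussion. That needs an assumed share of single-exam patients and an assumed effect per exam. It would also say nothing about the ICER, whose cost and effect parts may dilute together.
- A reader might infer that the budget impact will be under-costed. The article does not say which exam intensity it will use.
- A reader might conclude that repeated testing should become the primary exposure. That is a debatable trade. The Exclusion criteria remove patients with CAD. If this applies up to the index date, patients whose test revealed CAD leave the cohort, and a repeat-tested arm would be enriched for negative results.

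The article is condensed, so a fuller plan might hold ICERs by frequency class. The arm definition, the primary endpoint and the conclusions are nevertheless fixed here, and they do not match.

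**Conclusion.** The point holds as a mismatch between the stated question and the primary comparison. The primary ICER answers *at least one CAD test in 2008–2014 versus none*. The aim, the budget impact and the conclusions concern a routine programme, which the article's own survey puts at about 2.3 to 7 exams over the same 7 years against a threshold of one. The frequency subgroups as described do not bridge the two.

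The exam counts rest on physicians' reported frequencies being read as patient schedules. No size or direction is claimed for the effect on the ICER. The comparison is not invalid, but as worded its conclusion reaches beyond what it estimates. It should be put right before analysis.

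**What to change.** 1. Keep ever versus never as the primary comparison, but state the estimand, the objective it serves and the conclusions as *at least one CAD test in the selection period versus none*.
2. Define the frequency classes on exams in the selection period, before the index date, with no gap between them. State how frequency is counted: by average rate, at least one exam every three years means three or more exams in 7 years (7/3 = 2.3). Place patients with two exams explicitly. For each class, report incremental cost, life years and ICER against no screening as pre-specified secondary analyses.
3. Base the budget impact of systematic screening on the class or classes with at least one exam every three years, and show the pooled arm as a sensitivity analysis.

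This uses the Table 2 procedure codes already planned and needs no new data. The costs are wording changes, more analyses, and smaller and less precise classes. Class results need a caution that repeat-tested patients who are still free of CAD at the index date may be selected for negative tests.

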**Methods:**

SCADIAB is a comparative nationwide cohort study using data from the French National Health Data System. The main inclusion criteria are: age ≥ 40 years, DT2 diagnosed for ≥ 7 years, with ≥ 2 additional cardiovascular risk factors plus a history of microvascular or macrovascular disease, except CAD. We estimated ≥ 90,000 eligible participants for our study. Data will be extracted from 01/01/2008 to 31/12/2019. Eligible participants will be identified during a first 7-year selection period (2008–2015). Each participant will be assigned either in experimental (CAD screening procedure during the selection period) or control group (no CAD screening) on 01/01/2015, and followed for 5 years. The primary endpoint is the incremental cost per life year saved over 5 years in CAD screening group *versus* no CAD screening. The main secondary endpoints are: total 5-year direct costs of each strategy; incidence of major cardiovascular (acute coronary syndrome, hospitalization for heart failure, coronary revascularization or all-cause death), cerebrovascular (hospitalization for transient ischemic attack, stroke, or carotid revascularization) and lower-limb events (peripheral artery disease, ischemic diabetic foot, lower-limb revascularization or amputation); and the budget impact for the French Insurance system to promote the cost-effective strategy. Analyses will be adjusted for a high-dimension propensity score taking into account known and unknown confounders. SCADIAB has been funded by the French Ministry of Health and the protocol has been approved by the French ethic authorities. Data management and analyses will start in the second half of 2021.

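### Both arm definitions and the abstract give the exam window as 2008–2015, which conflicts with the stated close of selection on 31 December 2014; coded literally, exams in the first follow-up year would assign arms.

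*Protocol article*

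**What the plan says.** The Recruitment of participants and follow-up section fixes the timeline to the day:

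- Selection: "A selection period will be defined by the 7 years (January 1, 2008 to December 31, 2014) preceding the index date".
- Assignment: "Each participant will be assigned to one of the two study groups on the index date (January 1, 2015".
- Follow-up: "and then followed up to December 31, 2019".

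The exam criterion for each arm stands elsewhere, with a different end year. The Screening group section requires at least one listed exam "during the selection period (2008–2015". The No-screening group section takes "Participants who never experienced a screening exam as described above during the selection period (2008–2015), except resting electrocardiogram". The Methods paragraph of the abstract combines both forms: "Eligible participants will be identified during a first 7-year selection period (2008–2015", with assignment on 1 January 2015.

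The Statistical analysis plan section adds a related ambiguity. It relates screening frequency to survival through four subgroups, and the last is defined by a single exam within the follow-up period, not the selection period.

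**The concern.** The two group sections are the only places that say which exams make a patient screened or unscreened, and the procedure codes to be queried (Table 2) sit beside the printed years. The extract runs to the end of 2019, so 2015 exams will be in the data. No sentence says that exams from 1 January 2015 onward are ignored for assignment.

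A query on calendar years 2008 to 2015 would let exposure be decided after follow-up has begun. A patient first tested in, say, September 2015 would count as screened from 1 January, although that patient had to survive until September to qualify. A patient who died untested in March 2015 would stay in the control arm. Even with no effect of screening, the screening arm would then show fewer deaths and more life-years.

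This bears on the primary endpoint, whose denominator is incremental life-years over 5 years. The article's own summary of earlier trials reports no benefit of screening, so the true denominator may be close to zero, and a small false gain could then dominate the ratio. The high-dimension propensity score would not remove it: the score balances characteristics measured in the selection period, whereas the distortion comes from survival after the index date.

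**Working it through.** **Calendar check, from the dates in the article**

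| Window | Days | Years |
|---|---|---|
| 1 Jan 2008 to 31 Dec 2014 (Recruitment section) | 2,557 | 7.00 |
| 1 Jan 2008 to 31 Dec 2015 (2008–2015, inclusive) | 2,922 | 8.00 |
| Follow-up, 1 Jan 2015 to 31 Dec 2019 | 1,826 | 5.00 |

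The stated 7-year selection and 5-year follow-up are both reproduced. Inclusive years add 2,922 − 2,557 = 365 days. These are exactly the first follow-up year: 365/1,826 = 20% of the horizon.

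**Size, if the inclusive window were coded**

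All inputs here are assumptions; none is in the documents. There is no true effect. Annual mortality hazard *m* is 0.03, 0.05 or 0.08. The share screened before 2015, *s*, is 0.3 or 0.5. The probability of a first exam in 2015 among the unscreened, *q*, is 0.05, 0.10 or 0.20.

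Worked case: *m* = 0.05, *s* = 0.3, *q* = 0.10.

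1. Exam hazard λ = −ln(1 − 0.10) = 0.1054; *k* = λ + *m* = 0.1554.
2. Share of true controls who reach a 2015 exam alive: (λ/*k*)(1 − e^(−*k*)) = 0.0976. As a share of the cohort: 0.7 × 0.0976 = 6.8%.
3. Of these, *q*·e^(−5*m*) = 0.10 × 0.7788 = 0.0779 survive 5 years, so deaths are 0.0976 − 0.0779 = 0.0197.
4. Their person-years: after the exam, 0.0197/0.05 = 0.394. Before it (the immortal part), λ[1 − e^(−*k*)(1 + *k*)]/*k*² = 0.0476. Total 0.4416.
5. Without reclassification, each patient contributes 1 − e^(−0.25) = 0.2212 deaths and 0.2212/0.05 = 4.424 person-years.
6. Screening arm: deaths 0.3 × 0.2212 + 0.7 × 0.0197 = 0.0802; person-years 0.3 × 4.424 + 0.7 × 0.4416 = 1.636; rate 0.0490.
7. Control arm: deaths 0.7 × (0.2212 − 0.0197) = 0.1411; person-years 0.7 × (4.424 − 0.4416) = 2.788; rate 0.0506.
8. Rate ratio 0.0490/0.0506 = 0.97.
9. Life-years per patient: 1.636/0.3683 − 2.788/0.6317 = 4.443 − 4.413 = 0.03 in favour of screening, where 0.3683 = 0.3 + 0.7 × 0.0976 is the enlarged screening arm.

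The same formulas over all 18 combinations of inputs, and a simulation of 2,000,000 patients for each, agree on the ranges:

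- cohort share changing arm: about 2% to 14%;
- spurious 5-year mortality rate ratio: about 0.94 to 0.99;
- spurious life-years gained per patient: about 0.01 to 0.08.

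With the window closed on 31 December 2014, the overlap is 0 days and the null difference is zero apart from simulation noise.

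**The case against.** The strongest reply is that the article already resolves the point. The group sections do not create a separate exam window; they refer to the selection period, a term the Recruitment section defines to the day. The abstract calls that period 7-year, which inclusive years 2008 to 2015 cannot be. Assignment takes place on 1 January 2015, and the Strengths and limitations section also describes a 7-year period leading to assignment. An arm fixed on 1 January cannot depend on an exam later that year. This stands as to intent: 2008–2015 most likely means up to 1 January 2015. It does not make the printed years correct in the two places that set the exam criterion. The study design figure may show the timeline, but it is not available here.

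Two stronger readings should be resisted.

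- A reader might infer that the study will classify patients by 2015 exams. The documents do not support this; the anchors above point the other way.
- A reader might infer reverse causation, with a test prompted by a 2015 coronary event moving that event into the screening arm. That extends the window for exposure but not for eligibility. The same selection period identifies eligible patients, and the Exclusion criteria remove those with a history of acute coronary syndrome or coronary revascularization. A window applied consistently through 2015 would exclude such a patient. No figure for that mechanism is offered here.

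**Conclusion.** The conflict is real and lies in the date rule that defines exposure for the primary comparison: three places print 2008–2015 against the exact dates of the Recruitment section. It is an internal inconsistency with a probable benign explanation, not a chosen design with post-index exposure. The bias is conditional on the years being coded as inclusive. It would then favour screening, by a rate ratio of about 0.94 to 0.99 and about 0.01 to 0.08 life-years per patient, on inputs that are wholly assumed. That is modest in itself but could matter for a ratio whose denominator may be small. The subgroup defined by a single exam during follow-up shows that exposure timing is not otherwise beyond doubt. The correction should be made, because it is nearly free and uses the protocol's own dates.

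**What to change.** - In the abstract (Methods), the Screening group section and the No-screening group section, replace 2008–2015 with 1 January 2008 to 31 December 2014.
- Add one sentence: no exam dated on or after 1 January 2015 contributes to arm assignment.
- In the Statistical analysis plan section, reconcile the frequency subgroup defined by a single exam during follow-up with the same window.

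The cost is three date corrections, one added sentence and one clarified subgroup definition. The stated index date, follow-up and planned sample are unchanged.

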#### No-screening group

Participants who never experienced a screening exam as described above during the selection period (2008–2015), except resting electrocardiogram.

### Study endpoints

#### Primary endpoint

The incremental cost per life year saved over 5 years in CAD screening group *versus* no CAD screening.

### Secondary endpoints

#### Economic endpoints

(1) A cost-consequence analysis linking the total 5-year direct costs of each strategy (drugs, medical visits, hospitalizations, nursing visits, biological and radiological exams, technical exams, medical transports…) and the total number of major cardiovascular and renal events over 5 years; (2) the budget impact (in €) for the French Insurance system to promote the most cost-effective strategy between routine CAD screening and no screening; and (3) the total care consumption over the follow-up period.

